#### Primary Outcomes

##### Obesity-Related Outcomes

###### Body Weight

Body weight will be measured with a Tanita body composition analyzer (TBF-410), which is accurate to 0.1 kg. The scale will be cleared before each participant is weighed, and the participants will be asked to look straight ahead and stay still until the digital screen settles before the measurement is recorded. The data reliability can be further increased by using the same scale to measure all of the participants. Body weight will be measured at 3 time points and treated as a continuous variable. Changes in body weight, as an obesity-related outcome, will be calculated and compared between the IG and CG.

###### BMI

BMI scores will be calculated as weight divided by the square of height (ie, kg/m^2^). Measurement of weight is described in the section above. Height will be measured using a height gauge accurate to 0.1 cm (Harpenden Stadiometer, Holtain Ltd). When measuring heights, the participants will be asked to remove their shoes and stand straight, with knees and feet together. BMI will be evaluated at 3 time points and treated as a continuous variable. Changes in BMI, as an obesity-related outcome, will be calculated and compared between the IG and CG. BMI is also a categorical variable, which will be used for overweight and obese classification.

###### Waist Circumference

Waist circumference will be measured midway between the lowest rib margin and the top of the iliac crest at the end of a gentle expiration [50] using a flexible meter ribbon accurate to 0.1 cm. Waist circumference will be measured at 3 time points and treated as a continuous variable. Changes in waist circumference, as an obesity-related outcome, will be calculated and compared between the IG and CG. Waist circumference will also be used to estimate the waist-to-height ratio.

###### Hip Circumference

Hip circumference will be measured at the widest part of the body below the waist [51] using a flexible meter ribbon accurate to 0.1 cm. Hip circumference will be measured at 3 time points and treated as a continuous variable. Changes in hip circumference, as an obesity-related outcome, will be calculated and compared between the IG and CG.

###### Waist-to-Height Ratio

Waist-to-height ratio will be calculated as waist circumference divided by height. It will be evaluated at 3 time points and treated as a continuous variable. Changes in waist-to-height ratio, as an obesity-related outcome, will be calculated and compared between the IG and CG.

###### Body Fat Percentage

Body fat percentage will be estimated with the Tanita body composition analyzer (TBF-410) using foot-to-foot bioelectrical impedance analysis. After entering the participant’s gender, race, height, and age, the participant will be instructed to stand with bare feet on the metal footplates. The data will be displayed automatically. This variable will be estimated at 3 time points and treated as a continuous variable. Changes in body fat percentage, as an obesity-related outcome, will be calculated and compared between the IG and CG.

##### Fitness-Related Outcomes

###### 6-Minute Walk Test

The 6-minute walk test will be used to measure participants’ CPF. The test has been shown to have acceptable validity and reliability for adolescents and young adults with intellectual disability [52]. Testing procedures will follow the study protocol of Chow et al [53]. Participants will be instructed and encouraged to cover the greatest possible distance on a flat surface 25 m in length. They will be instructed to keep a steady pace, whether running or walking. A trained examiner will measure and record the distance covered by each participant. Each participant will be assigned a trained partner (university student helper) based on the participant’s special physical condition and cognitive ability to receive verbal direction and encouragement during the test. The 6-minute walk test will be performed at 3 time points, and the distance covered will be treated as a continuous variable. Changes in distance, as a fitness-related outcome, will be calculated and compared between the IG and CG.

###### Number of Stands in 30-Second Sit-to-Stand Test

A 30-second sit-to-stand test will be used to assess participants’ lower limb strength and endurance. It measures the maximum number of times a participant can rise to a full standing position from a seated position in a 30-second period, without pushing off with their arms. This test is administered using a chair with a seat height of approximately 35.6 cm, without arms. The participants will be instructed to sit with back straight and feet approximately shoulder-width apart and placed on the floor. Arms will be guided to be crossed at the wrists and held against the chest. The number of completed stands will be recorded. This test was first developed for older adults and is highly correlated with strength of the lower limbs [54]. A high correlation of the test score with the strength of the lower limbs (*r*=0.69) has also been found for adolescent children with intellectual disability [33,52]. The number of stands within a 30-second period will be measured at 3 time points and treated as a continuous variable. Changes in the number of stands, as a fitness-related outcome, will be calculated and compared between the IG and CG.

###### Number of Sit-Ups in 1 Minute

A 1-minute sit-up test will be adopted to evaluate participants’ abdominal muscular strength and endurance. The task requires participants to perform as many sit-ups as possible in 1 minute or until the participant experiences muscle fatigue and cannot perform any more. Participants will be instructed to cross their arms on their chests with hands on shoulders, tighten their abdominal muscles, and rise up to touch elbows to thighs. Then, they will return to the start position and repeat [55]. The number of sit-ups completed in 1 minute will be measured at 3 time points and treated as a continuous variable. Changes in the number of sit-ups, as a fitness-related outcome, will be calculated and compared between the IG and CG.

###### Handgrip Strength

The handgrip strength test will be used to assess participants’ hand and forearm muscular strength. During the test, the participant will be instructed to adopt a standing position with arms at his/her side, not touching the body. The participant will be asked to squeeze the instrument with as much force as possible for 10-20 seconds. Right and left hands will be alternated [36]. Handgrip strength will be measured at 3 time points and treated as a continuous variable. Changes in handgrip strength, as a fitness-related outcome, will be calculated and compared between the IG and CG.

###### Sit-and-Reach Distance

For the sit-and-reach test, each participant will begin by removing his/her shoes and sitting down at the test apparatus. One leg will be fully extended with the foot flat against the end of the testing instrument. The other knee will be bent, with the sole of the foot flat on the floor 5 cm to 8 cm to the side of the straight knee. The arms will be extended forward over the measuring scale with hands palms down, one on top of the other. Each participant will be instructed to reach directly forward with both hands along the scale 4 times and to hold the position of the fourth reach for at least 1 second. After measuring one side, the participant will be asked to switch the position of his/her legs and reach again [55]. The distance of the sit and reach will be measured at 3 time points and treated as a continuous variable. Changes in the distance of the sit and reach, as a fitness-related outcome, will be calculated and compared between the IG and CG.

#### Secondary Outcome

##### Blood Pressure

The participants’ systolic and diastolic blood pressure will be measured using an Omron blood pressure monitor (calibrated before using). During the test, the participant will be asked to sit quietly for approximately 5 minutes and then remove outer garments and roll up their shirtsleeves, if necessary, to bare the upper right arm. The measurements will be taken on the right arm. The participant’s arm will be resting on the desk so that the antecubital fossa is at the level of the heart, with the palm relaxed and facing upward. Then, the cuff will be placed on the right arm, with the bottom edge 1 cm to 2 cm above the antecubital fossa. The top edge of the cuff cannot be restricted by clothing. Two measurements will be taken 1 minute apart, and the readings will be recorded. Before and during the measurement, it is necessary for the participant to be calm [56]. Blood pressure will be measured at 3 time points and treated as a continuous variable. Changes in blood pressure will be calculated and compared between the IG and CG.

#### Confounding Variables

##### Subjective Measurements of PA Level, Screen Time, Sleep Duration, Eating Habits, and Pubertal Stage

Subjective data on participants’ PA level, screen time, sleep duration, eating habits, and pubertal stage will be collected using a self-report questionnaire. As the participants may not be able to fully understand questionnaires independently, the participants and their parents will complete the questionnaire together at home. In addition, to increase the reliability of the responses regarding participants’ school activities and snacks, a short version of the self-report questionnaire will be administered to the participant’s schoolteacher. Subjective PA level, screen time, sleep duration, eating habits, and pubertal stage will be collected at 3 time points and treated as confounding variables. They will be used as controls in the data analysis.

The Chinese version of the Global Physical Activity Questionnaire (GPAQ) will be modified to estimate participants’ PA and sedentary behaviors. The modified GPAQ will contain 12 items to ask about the frequencies and duration of moderate and vigorous PA in school, transport, and leisure time situations in a typical week. There will be 2 additional questions about sedentary behaviors in a typical week. Furthermore, we will add questions about screen time (2 items) and sleep duration (2 items) on a typical weekday and on weekends. The average daily time spent performing MVPA will be calculated for the participants and used to divide them into 2 groups (active versus inactive) based on the PA level for children recommended by the World Health Organization (ie, 60 minutes/day). For sedentary behaviors, a cutoff point of 4 hours/day will be adopted to distinguish the 2 groups. The average sleep duration will also be used to divide the participants into 2 groups (sufficient versus insufficient, with a cutoff point of 8 hours/day) [57].

Questions about participants’ eating habits will be adapted from a dietary questionnaire developed by the Central Health Education Unit of Hong Kong for school-aged children [58]. The questionnaire will feature 9 items to evaluate the frequency of food consumption, including the consumption of fruits, vegetables, meats, fish, eggs, beans, grains, fried foods, sweetened drinks, high-sugar foods, high-salt foods, and high-fat foods. The questionnaire will also include 4 items to measure eating habits at breakfast and dinner. In addition, we have adopted questions about snacks (3 items) and fast foods (1 item) from a dietary questionnaire for children that was developed by the Pennsylvania Department of Health [59].

Puberty is a dynamic process of development marked by rapid changes in body composition and health outcomes [60]. Adolescents of the same age may differ in the rate of their physical growth [61]. Research suggests that Tanner staging from a clinical assessment is the gold standard measurement of puberty status [61]. The Tanner staging system consists of 5 stages, separately designed for boys and girls, which are determined by pubic hair growth in both sexes, breast development in girls, and testicular development in boys [62]. However, this kind of assessment is challenging in school settings. As a result, the self-assessment of puberty status might be more acceptable to the participants [60]. In this study, an illustrated Tanner pubertal questionnaire will be provided to participants to collect the information regarding pubertal stage [63].

### Process Evaluation

Process evaluation will be used to monitor and document the implementation of the intervention [61]. A framework model for designing a process evaluation of RCTs will be adopted. Participants’ retention rate, adherence rate, and compliance to the intervention will be assessed. Moreover, all participants will be asked about their satisfaction with the intervention, perceived effectiveness and usefulness of the intervention, future participation intention, and intention to recommend the intervention to others in a 5-point Likert scale questionnaire [64].

### Quality Control

Manual and operational procedures will be prepared for all of the team members. Three training sessions (60 minutes/session) will be provided. Monthly and ad hoc research meetings with experts (university teachers) in the PA area, student helpers, and PE teachers/nurses in the special schools will be held to ensure the success of the proposed study. To promote a uniformly high performance, we will conduct unannounced quality assurance inspections (2 times/month) in the field. The data will be checked by auditors immediately and entered twice to enhance accuracy. Moreover, on the written informed consent form, we will request that the participants in the IG and their parents do not communicate with any parents and classmates in the school about the intervention to avoid contamination and behavioral spillover. In addition, we will seek the participating schools’ help to remind them and monitor and prevent occurrences of such behavior.

### Data Collection Procedure

Once participants have been recruited, informed consent forms and questionnaires will be sent to the participants. They will be completed by the parents with the assistance of the participants within 1 week and returned to their schoolteachers. To ensure the confidentiality of the personal information, these files will be sealed in an envelope. The parents of the participants who do not send back the forms will be contacted via a phone call or text message. New documents will be prepared and sent to the parents if the documents have been lost or mislaid.

After collecting the required documents, we will arrange a morning session to conduct the obesity- and fitness-related tests and blood pressure measures for the participants. The test procedure is as follows: heart rate test and blood pressure measurement first, then the obesity-related tests, and finally the fitness-related tests. The 6-minute walk will be the last fitness test. If a participant is absent on the test day, another test session will be arranged after consultation with the school.

### Data Analysis

SPSS Statistics (version 23.0; IBM Corp) will be used for the data analysis. Mean (SD) and/or median (IQR) values will be calculated for the continuous variables (eg, BMI). All of the continuous variables at T1 will be tested for between-group differences using an independent sample *t* test. Normality will be checked using Q-Q plots and tested for equal variance, as assessed by Levene’s test. If skewed, the data will be logarithmically transformed before the *t* test is applied. A repeated measures analysis of variance will be used to test for significant differences in the changes in the continuous outcome variables between the 2 groups, where group and time are the 2 factors of interest and will be controlled for significant confounding factors (eg, age). The variables will be selected in a stepwise manner, and only those with *P*<.1 will be kept in the final models. A significance level of .05 will be adopted (2-tailed test). Intention-to-treat analysis will be adopted and performed to avoid bias from withdrawals or protocol deviations.

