Hence, given the above evidence, we conducted a systematic review and meta-analysis on this topic (data have not yet been published). Our findings suggested the following: (1) PA was the predominant component to be adopted into interventions, with 27 of the 29 identified interventions implementing PA; (2) PA contributes to improving CPF (50.50 m, 95% CI 22.23-78.77; *P*<.001), lower limb muscular strength (19.41 kg, 95% CI 11.32-27.49; *P*<.001), and upper limb muscular strength (4.42 kg, 95% CI 0.12-8.73; *P*=0.04) in children with intellectual disability; and (3) the limited research related to this population prevented us from drawing any confirmed conclusions on relationships with obesity.

In relation to the above, we would like to develop a PA intervention to reduce obesity and improve HRPF levels in adolescents with intellectual disability. The proposed study will be a 12-week, school-based PA program with a 2-armed randomized controlled trial (RCT) design. The primary outcomes will be obesity- and HRPF-related outcomes. Blood pressure will be evaluated as a secondary outcome, as some common noncommunicable diseases, such as hypertension and diabetes, that occur in adulthood have become more prevalent in children, mainly due to unhealthy lifestyles and obesity [15]. The objectives of the proposed study are to evaluate the effectiveness of the intervention on obesity- and HRPF-related outcomes (primary outcomes) and blood pressure (secondary outcome) and to evaluate sustainable effects of the intervention on all outcomes, with a comparison with a control group (CG) and adjusted for confounding factors (eg, sociodemographic and lifestyle factors).

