#### Sample Size Estimation

The sample size will be calculated using G*Power software (version 3.1.9.4). Previous research has shown that a medium effect size of 0.21 is appropriate [17]. Setting a significance level of *P*<.05, a power level of 80%, and a constant correlation of 0.5, and assuming a 20% dropout rate, a total sample size of 48 participants (24 participants in each group) will be needed.

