### Measures

Obesity- and fitness-related outcomes will be measured as the primary outcomes. Blood pressure will be a secondary outcome. The participants’ demographic information will be collected at baseline and used as a control in data analysis. Moreover, other potential confounders, such as subjective PA level, screen time, sleep duration, eating habits, and pubertal stage, will also be collected and used as controls in data analysis. All of the measurements, except the demographic data, will be collected at baseline (T1), postintervention (T2), and at the 12-week follow-up (T3). A set of evaluation instruments has been drafted.

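### The one planned group-by-time test does not by itself support a claim of sustained effect; baseline-adjusted T2 and T3 contrasts would answer the two objectives separately and more precisely

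*Protocol article*

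**What the plan says.** The last paragraph of the Introduction sets two aims: "to evaluate the effectiveness of the intervention on obesity- and HRPF-related outcomes (primary outcomes) and blood pressure (secondary outcome"), and separately "to evaluate sustainable effects of the intervention on all outcomes". Study Design schedules the follow-up test 12 weeks after the programme for the second aim. Under Measures, the outcomes "will be collected at baseline (T1), postintervention (T2), and at the 12-week follow-up (T3").

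Data Analysis gives one method for between-group effects, a repeated measures ANOVA that compares the arms on change in each continuous outcome. Of the terms in that model it says: "where group and time are the 2 factors of interest and will be controlled for significant confounding factors (eg, age"). Neither a T2 nor a T3 contrast is named. The covariates are confounders kept by stepwise selection; the T1 value of the outcome is not among those named.

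The outcome sections use a common form, for example "Changes in body weight, as an obesity-related outcome, will be calculated and compared between the IG and CG". They do not say between which visits the change is taken.

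Sample Size Estimation gives the planning values: "Previous research has shown that a medium effect size of 0.21 is appropriate". The remaining settings follow in the same section: "Setting a significance level of *P*<.05, a power level of 80%, and a constant correlation of 0.5, and assuming a 20% dropout rate". The result is 48 participants, 24 per group.

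**The concern.** Two questions share one stated test. With three time levels, a group-by-time test asks only whether the two mean profiles are parallel. Any departure counts: a gain at T2 that persists, a gain at T2 that has gone by T3, or a difference that appears only at T3. If the interaction P value is the basis for inference, a significant result does not say which of these happened, yet the second objective depends on exactly that.

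The use of T1 is a separate, smaller matter. Randomised arms have the same expected baseline. Treating T1 as one more response, or subtracting it to form a change, does not use that fact. Adjusting for T1 does, and it gives a more precise estimate from the same data.

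**Working it through.** **Inputs.** From Sample Size Estimation: effect size 0.21, alpha 0.05, power 80%, constant correlation rho = 0.5, dropout 20%, total 48. From Data Analysis: two-tailed testing. From Measures: three time points. Assumption: 0.21 is Cohen's f, the effect-size metric of G*Power for analysis of variance.

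**1. Reproduce the sample size.** For the within-between interaction with k = 2 groups and m = 3 times:

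- lambda = f² × N × m / (1 − rho) = 0.0441 × 38 × 3 / 0.5 = 10.05
- df1 = (k − 1)(m − 1) = 2; df2 = (N − k)(m − 1) = 72
- power = 0.8003 at N = 38; 38 / 0.8 = 47.5, rounded up to 48

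This is the protocol's figure. Two time levels give 48 before dropout and 60 after; a between-group main effect with three levels gives 122 and 153. Neither fits. The within-subject time test also gives 38, but Data Analysis asks about differences between groups in change, so the interaction is the natural reading. T1 is then one of three response levels and the test has 2 df.

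**2. Translate f into a group difference.** Let the arm differences at T1, T2 and T3 be g = (0, a, b) in SD units. Then f² is the mean over visits of [(g − mean g)/2]².

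- Sustained, (0, d, d): half-deviations (−d/3, d/6, d/6), sum of squares d²/6, so f² = d²/18
- Lost by T3, (0, d, 0): half-deviations (−d/6, d/3, −d/6), sum of squares d²/6, so f² = d²/18
- T3 only, (0, 0, d): the same by symmetry

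In all three, d = 0.21 × √18 = 0.891. Lambda is identical, so power is identical.

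| True pattern | d at T2, T3 | Interaction power, N = 38 | T3 power, change score | T3 power, adjusted for T1 |
|---|---|---|---|---|
| Sustained | 0.89, 0.89 | 0.80 | 0.76 | 0.87 |
| Half retained | 1.03, 0.51 | 0.80 | 0.34 | 0.43 |
| Lost by T3 | 0.89, 0 | 0.80 | 0.05 | 0.05 |
| T3 only | 0, 0.89 | 0.80 | 0.76 | 0.87 |

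Simulation (20,000 runs each, equal correlations, N = 38) gave 0.80 for the sustained, lost and T3-only patterns, and a type I error of 0.050.

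**3. Precision at one visit.** Per-participant variance, with SD = 1:

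- T1 ignored: 1
- change score: 2(1 − rho) = 1.00 at rho = 0.5
- adjusted for T1: 1 − rho² = 0.75 at rho = 0.5
- ratio, adjusted to change: (1 + rho)/2 = 0.75, 0.85, 0.90 and 0.95 at rho = 0.5, 0.7, 0.8 and 0.9

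For T2 with d = 0.891 and 38 completers, the noncentrality is d / √(4v/38):

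- change score: 0.891 / √(4 × 1.00/38) = 2.75, power 0.762
- adjusted: 0.891 / √(4 × 0.75/38) = 3.17, power 0.869

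With all 48 completing, the powers are 0.856 and 0.937.

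**The case against.** The strongest reply is that the planned model can answer both questions. A group-by-time analysis over T1, T2 and T3 also yields the T1-to-T2 and T1-to-T3 group contrasts. The outcome sections speak of comparing changes, which could mean visit by visit, and an analysis plan that is not shown may name the contrasts. Nothing says that a significant interaction will be reported as a sustained effect, and visit-by-visit summaries would let a reader see an effect fade. This stands as far as it goes. A reader might infer that the analysis cannot separate T2 from T3; the protocol does not support that. What remains is that the test it states, and for which its sample size reproduces, is not tied to either objective.

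A reader might also infer that the test is invalid, or that the baseline measurement is wasted. Neither follows. Under equal correlations the type I error is 5%, and 48 participants is the right number for this test. A change-based analysis is valid in a randomised trial. It adds no precision over ignoring T1 only at the planning correlation of 0.5; at 0.8 to 0.9 it comes within 5% to 10% of the adjusted variance. Such correlations are plausible for weight or BMI, but that is an assumption.

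Two further points stand. The Introduction does not rank T2 above T3, so no such ranking should be imposed. Two contrasts on each of the 11 primary outcomes make 22 tests, which adds multiplicity.

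**Conclusion.** The point holds as a matter of interpretation and efficiency, not validity. The interaction test has its stated 80% power, but that power is the same for a fully sustained effect and for one fully lost by T3. If half the effect is retained, the interaction keeps 0.80 power while a T3 contrast has 0.34 to 0.43. The interaction P value alone therefore does not support a claim of sustained effect.

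The gain from adjusting for T1 is real but depends on correlation: 25% of the change-score variance at rho = 0.5, and 5% to 10% at 0.8 to 0.9. The T2 powers of 0.87 and 0.76 compare two ways of testing the same contrast. The interaction's 0.80 belongs to a different hypothesis and should not be set against them as a like-for-like loss.

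These results assume that 0.21 is Cohen's f (hence 0.89 SD, a figure the protocol does not state), equal correlations, and 38 completers. The three-level, 2-df reading is inferred from the sample size and the analysis wording. The plan should be changed because the improvement is free, not because the trial would otherwise fail.

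**What to change.** In Data Analysis, state for each continuous outcome:

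- **Effectiveness:** the arm difference at T2, adjusted for the T1 value, with a 95% confidence interval.
- **Sustained effect:** the arm difference at T3, adjusted for the T1 value, with a 95% confidence interval. The conclusion about sustained effect rests on this contrast.

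Either ANCOVA at each visit or a mixed model with a common T1 mean will do. Enter the T1 value always, outside the stepwise selection.

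The interaction test may stay as a supporting test or as a gate that must be passed before the two contrasts are tested. As a gate it limits the added multiplicity within an outcome, though not across the 11 primary outcomes. A gated claim cannot have more power than the gate itself, 0.80 under the planning values with 38 completers.

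The cost is a few sentences of analysis text, best settled before outcome data are analysed by arm. No new visits, measurements or participants are needed, and 48 remains adequate: with 38 completers and d = 0.89, each adjusted contrast has power 0.87 when no gate is used.

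### Covariates for the primary analysis are picked stepwise at P<.1 from an open list, so the adjusted model is not fixed in advance and the two-sided .05 level is not guaranteed

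*Protocol article*

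**What the plan says.** All statements are in the protocol article.

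- **Model (Data Analysis).** "A repeated measures analysis of variance will be used to test for significant differences in the changes in the continuous outcome variables", with group and time as the factors. The analysis "will be controlled for significant confounding factors (eg, age"; age is only an example.
- **Selection rule (Data Analysis).** "The variables will be selected in a stepwise manner", and "only those with *P*<.1 will be kept in the final models".
- **Level (Data Analysis).** "A significance level of .05 will be adopted (2-tailed test").
- **Candidates (Measures).** Demographic information and "other potential confounders, such as subjective PA level, screen time, sleep duration, eating habits, and pubertal stage". The words *such as* leave the list open.
- **Timing (Confounding Variables).** The lifestyle and pubertal variables are recorded at T1, T2 and T3, and the section does not say which values may enter a model.

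The article does not say whether selection is forward or backward, whether group and time stay in the model while covariates are being selected, or whether selection is run once or for each outcome.

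**The concern.** This is a rule that the article states, not a detail left to an analysis plan. It lets the trial's own data decide what the primary comparison is adjusted for. The final ANOVA then reports P values and confidence intervals as if that covariate set had been fixed beforehand. With a small sample and many candidates, some covariates stay in by chance. If they are chosen because they explain residual variation around the group comparison, the residual variance tends to come out too small and the test rejects too often.

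The estimate is also affected. The adjusted effect depends on which covariates happened to pass P<.1, and even age can drop out. With 11 primary outcomes, readers could face 11 effects adjusted for different things for no reason stated in advance.

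**Working it through.** **1. Sample size basis.** Inputs from Sample Size Estimation: effect size 0.21 (taken as Cohen's f), power 80%, correlation 0.5, alpha .05, dropout 20%. For the group-by-time interaction with k = 2 groups and m = 3 time points:

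λ = f²·N·m/(1−ρ) = 0.0441 × 38 × 3/0.5 = 10.05, with df = 2 and 2 × (38−2) = 72.

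Power is 0.800 at N = 38, and 38/0.8 = 47.5, rounded up to 48. The stated 48 is reproduced, so 38 and 48 bracket the number likely to be analysed.

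**2. Type I error after selection.** The simulation had no intervention effect and tested group-by-time at .05 after stepwise selection at P<.1. It used 3,000 runs per setting, so the Monte Carlo standard error is √(0.05 × 0.95/3000) ≈ 0.004. Assumptions, because the article gives no figures: 8 or 12 independent baseline candidates, which together explain 0% or 30% of the change. Each cell shows forward / backward selection.

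| N | Candidates | Variance explained | Group in selection model | Selection ignores group |
|---|---|---|---|---|
| 38 | 8 | 0% | 6.5% / 5.9% | 4.5% / 5.3% |
| 38 | 8 | 30% | 6.6% / 6.4% | 5.1% / 4.7% |
| 38 | 12 | 0% | 7.6% / 7.7% | 5.4% / 5.1% |
| 38 | 12 | 30% | 7.2% / 8.3% | 4.7% / 5.3% |
| 48 | 8 | 0% | 6.2% / 6.2% | 5.1% / 4.8% |
| 48 | 8 | 30% | 6.1% / 6.0% | 5.2% / 5.0% |
| 48 | 12 | 0% | 6.0% / 6.1% | 4.7% / 5.0% |
| 48 | 12 | 30% | 6.7% / 7.3% | 4.6% / 5.5% |

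With all 8 or 12 candidates kept as a fixed set, the error was 4.2% to 5.6%. Any excess therefore comes from the selection, not from adjusting.

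**3. A longer candidate list.** A simpler simulation of one change score, with pure-noise candidates and group in the selection model, gave for 8, 12 and 16 candidates 6.7%, 7.9% and 8.9% at N = 38, and 5.9%, 7.0% and 9.2% at N = 48. When selection ignored group, the error was again about 5%.

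**4. Agreement of models across outcomes.** The article lists 6 obesity-related and 5 fitness-related primary outcomes, 11 in all. Selection was run separately for each, with 8 candidates, N = 38 and pairwise outcome correlations of 0.3 or 0.7 (assumed), 150 runs per setting. The mean number of distinct covariate sets was 4.9 to 7.9. All 11 outcomes shared one set in at most 0.7% of runs.

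**The case against.** The strongest reply is that the error rate need not rise at all. If covariates are selected without group in the model, the simulated level is 4.5% to 5.5%, and the article does not rule that procedure out. A reader might infer that the rule invalidates the .05 level. The documents do not support that, because the result depends on a step they leave unstated. The number of candidates is also assumed, and 16 pure-noise candidates is an unfavourable case, since age and pubertal stage probably matter for weight and fitness. The article plans an intention-to-treat analysis, so 38 participants is a lower bound rather than the planned analysis set. This is why results at 48 are shown as well.

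Other stronger readings also go beyond the text:

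- **Selection for each outcome.** A separate selection per outcome is a natural inference from one ANOVA per outcome and the plural *models*, but it is not stated.
- **T1 tests.** The article says "All of the continuous variables at T1 will be tested for between-group differences using an independent sample" *t* test. A reader might take these tests to drive the covariate choice. The article makes no such link, and as described the tests change no effect estimate.
- **Dichotomised covariates.** Average MVPA time will be "used to divide them into 2 groups (active versus inactive"), and sedentary time and sleep are split similarly. The article does not say that the split versions are what enter the model.

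What remains is that the primary model is not fixed in advance. That holds under either reading of the selection step.

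**Conclusion.** The point holds in a limited form and should be corrected. The primary adjusted model is chosen from the data out of an open list, and control of the two-sided .05 level depends on an unstated detail. The size is modest: about 6% to 8% per test if group is in the selection model with 8 to 12 candidates, about 9% with 16, and about 5% if selection ignores group. These figures assume independent baseline candidates and 38 to 48 participants. They are per test and do not address multiplicity over the 11 outcomes.

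If selection is run for each outcome, different covariate sets across the primary outcomes are close to certain under the assumptions used. Possible adjustment for T2 or T3 values of physical activity, screen time, sleep or eating habits, which the intervention could change, is not quantified here.

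**What to change.** Delete the stepwise P<.1 rule. Name one short set of baseline (T1) covariates, the same for every primary outcome and kept whatever their P values, for example age and sex. Limit any further covariate to its T1 value. Label any stepwise model as a sensitivity analysis only.

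If adjustment for the T1 value of the outcome is wanted, model T2 and T3 (or the changes from T1) with T1 as a covariate. T1 is already one of the repeated responses in the planned ANOVA and should not be both response and covariate. If this route is taken, the sample size paragraph should say so, because the stated 48 reproduces for a group-by-time interaction over three time points.

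School should not be forced in as a term unless the number of schools is small and known; the article does not give it.

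Cost: analysis wording and a few degrees of freedom. No new data are needed, and fixing the covariates does not itself change the sample size of 48.
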